## **10 DIRECT ACCESS TO SOURCE DATA**

The investigator will permit monitoring and reviews by the ethics committee and authorized representatives of the medical governmental regulatory authorities providing direct access to source data and source documents for the purposes of quality assurance and evaluation of the study safety and progress.

All protocol required clinical information and source data (e.g., blood results) will be collected in Case Report Forms (CRFs) designed by the investigator, that might serve as source documents.

## **11 QUALITY CONTROL AND QUALITY ASSURANCE**

The trial will be monitored by the internal trial monitor. The trial monitor will perform monitoring site visits before and throughout the trial. The purpose of the visits includes to ensuring protocol adherence, accurate capture of clinical data, and appropriate documentation in the Master File.

## 12 ETHICS

This protocol will be approved by the joint Gambia Government/MRC Ethics Committee before this trial commences. The trial will be conducted in full conformity with the principles set forth in the current revision of the Declaration of Helsinki, International Ethical Guidelines for Biomedical Research Involving Human Subjects (2002), and the MRC Ethics Guide (2004).

For potential risks and benefits see Section 2.3.

### 12.1 Informed Consent Process

Oral informed consent will be obtained from all participants prior to screening.

Either the study physician or a field worker will explain the study to the potential volunteer, outlining the potential risks, and will answer questions that may arise. If they agree to take part, written informed consent will be obtained from all participants prior to enrolment. The consent form to be used will have been approved by the ethics committee. In any participant without fluent English language skills, a translation in their own language will be provided. A copy of the informed consent document will be given to the subjects for their records.

The subjects may withdraw consent at any time throughout the course of the trial. The rights and welfare of the infants will be protected by emphasizing to the parents that the quality of their medical care will not be adversely affected if they decline to participate in this study.

### 12.2 Subject Confidentiality

Blood samples and Case Report Forms will be coded by initials and hospital number only.

Section 1 of the CRF used by the fieldworkers will have the volunteer's personal details, and will be stored together with the signed copies of the consent form separately from the other parts of the CRF, in a locked filing cabinet. Sections 2-3 of the CRF will be identifiable by the study participants ID number only, and will be stored separately in a locked filing cabinet

All records will be kept in a locked filing cabinet, which is accessed only by the listed investigators. All computer entry and networking programs will be done with coded numbers only. Only authorized persons will have access to the data (see section 10)  
Signed consent forms will be stored separately from other records in a locked filing cabinet in a secure office.

Every effort will be taken to maintain confidentiality. Clinical information will not be released without

written permission of the participants with the exceptions stated in Section 10.

### **12.3 Biohazard Containment**

As the transmission of HIV and other blood-borne pathogens can occur through contact with contaminated needles, blood, and blood products, appropriate blood and secretion precautions will be employed by all personnel in the drawing of blood and shipping and handling of all specimens for this study, according to the MRC safety manual.

## 13 DATA HANDLING AND RECORD KEEPING

The investigators will maintain appropriate medical and research records for this trial. The investigator is responsible to ensure the accuracy, completeness, legibility, and timeliness of the data reported. All source documents should be completed in a neat, legible manner to ensure accurate interpretation of data.

All data on the Case Report Forms must be legibly recorded in blue or black ink or typed. A correction should be made by striking through the incorrect entry with a single line and entering the correct information adjacent to it. The correction must be initialed and dated by the investigator or a designated, qualified individual.

Any requested information that is not obtained as specified in the protocol should have an explanation noted on the CRF as to why the required information was not obtained. All source documents and laboratory reports must be reviewed by the clinical team and data entry staff, who will ensure that they are accurate and complete.

For confidentiality of data see Section 12.2.

The data manager will be responsible for receiving, entering, cleaning, querying, analyzing and storing all data that accrues from the trial.

Clinical data including AEs and clinical laboratory data will be entered into Microsoft Access. The data system includes password protection and internal quality checks, such as automatic range checks, to identify data that appear inconsistent, incomplete, or inaccurate. Clinical data will be entered directly from the source documents.

Data for this trial will include laboratory and safety measures.

All records pertaining to this study will be kept for a period of at least 10 years before destruction.

### Protocol Deviations

The investigator will conduct the trial in compliance with the protocol which was given approval by the ethics committee.

The investigator will not implement any deviation from or changes of the protocol without prior review and documented approval from the ethics committee of an amendment, except where necessary to eliminate an immediate hazard(s) to trial subjects, or when the change(s) involve only logistical or administrative aspects of the trial (e.g., change in monitor(s), change of telephone number(s)).

**Clinical Trial: Charcoal**

---

The investigator, or person designated by the investigator, will document and explain any deviation from the approved protocol in the protocol deviation file.

A protocol deviation is any noncompliance with the clinical trial protocol, Good Clinical Practice (GCP), or other defined procedures requirements. The noncompliance may be either on the part of the subject, the investigator, or the study site staff. As a result of deviations, corrective actions are to be developed by the site and implemented promptly.

The investigator may implement a deviation from or a change of the protocol to eliminate an immediate hazard(s) to trial subjects without prior ethics approval. As soon as possible, the implemented deviation or change, the reasons for it, and, if appropriate, the proposed protocol amendment(s) should be submitted to the ethics committee for review and approval.

It is the responsibility of the site to use continuous vigilance to identify and report deviations.

## 14 INDEMNITY

In case of any harm as a direct result of participating in the trial medical care and treatment will be provided for free.

## 15 PLANS FOR DISTRIBUTION OF RESEARCH FINDINGS

At the end of the study, a research report of the methods, detailed results, and brief conclusions will be prepared. These data are a prerequisite for the design of further studies that aim to explore the efficacy of such an approach in mild cases of malaria, and eventually in severely ill patients.

Unit seminars will be given, and data may be presented on scientific conferences.

**APPENDIX A: SUMMARY PARTICIPANT SCHEDULE**

| Time                                  | Procedure                                                                                                                                                                                                                                                               |
|----------------------------------------------|--------------------------------------------------------------------------------------------------------------------------------------------------------------------------------------------------------------------------------------------------------------------------------|
| 0h – evening day 0
(Time point 1) | 
 
- Clinical assessment by qualified physician
 
- FBC, Full Biochemistry, Thick film
 
- IV artesunate to all subjects
 
- Plain water to subjects in group 1
 
- AC to subjects in group 2 only,
 
 |
| 1h ± 5min*
(Time point 1b)        | 
 
- AC to subjects in group 3 only
 
                                                                                                                                                                                             |
| 12h ± 5min*
(Time point 2)        | 
 
- Clinical assessment by qualified physician
 
- 2nd dose of IV artesunate to all subjects
 
- Plain water to subjects in group 1
 
- AC to subjects in group 2 only
 
                         |
| 12h 5 min*
(Time point 3)         | 
 
- Serum Creatinine, Albumin
 
- Plasma Artesunate, DHA
 
                                                                                                                                                                |
| 12h 10 min*
(Time point 4)        | 
 
- Serum Creatinine, Albumin.
 
- Plasma Artesunate, DHA
 
                                                                                                                                                               |
| 12h 15 min*
(Time point 5)        | 
 
- Serum Creatinine, Albumin.
 
- Plasma Artesunate, DHA
 
                                                                                                                                                               |
| 12h 30 min*
(Time point 6)        | 
 
- Serum Creatinine, Albumin.
 
- Plasma Artesunate, DHA
 
                                                                                                                                                               |
| 13h ± 5min*
(Time point 7)        | 
 
- Serum Creatinine, Albumin.
 
- Plasma Artesunate, DHA
 
- AC to subjects in group 3 only
 
                                                                                                                     |
| 13h 30 min ± 5min*
(Time point 8) | 
 
- Serum Creatinine, Albumin.
 
- Plasma Artesunate, DHA
 
                                                                                                                                                               |
| 15h ± 5min*
(Time point 9)        | 
 
- Serum Creatinine, Albumin.
 
- Plasma Artesunate, DHA
 
                                                                                                                                                               |
| 18h ± 5min*
(Time point 10)       | 
 
- Full biochemistry
 
- Plasma Artesunate, DHA
 
                                                                                                                                                                        |
| 18h 5min – 24hrs                      | 
 
- Clinical assessment by qualified physician
 
- Discharge
 
                                                                                                                                                            |

\* All time points measured from the time of the first dose of IV artesunate.

For details see Section 7.

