#### 3.2 Trial Endpoints

The plasma levels of artesunate and its metabolite DHA as well as para-aminobenzoic acid (PABA) will be measured by liquid chromatography – mass spectrometry (LC-MS) at the time points 5, 10, 15, 30, 60, 90 min and 3 and 6 hours after the second dose of artesunate has been given (at 12 hours) to determine their  $C_{max}$ ,  $t_{max}$ ,  $t_{1/2}$  and AUC.

Creatinine and albumine will be measured too. These parameters are necessary to calculate renal clearance and binding of the drug to plasma proteins.

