**Plasma level determination**

Plasma samples will be collected to determine the levels of artesunate and its metabolite DHA as well as para-aminobenzoic acid (PABA) at the time points 5, 10, 15, 30, 60, 90 min and 3 and 6 hours after the second dose of artesunate has been given. Samples will be frozen immediately and stored in LiN2 at the MRC field station nearby, and will be transported on dry ice via Fajara to the London School of Hygiene and Tropical Medicine in the UK. Here, samples will be analyzed by liquid chromatography – mass spectrometry (LC-MS)

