## 9 STATISTICAL CONSIDERATIONS

The statistical methods and analysis will be described in detail in the statistical plan.

The primary endpoint is the area under each subject's artesunate (ARS) concentration-time curve (AUC). Secondary endpoints are a) the maximum concentration ( $C_{max}$ ), time to reach maximum concentration ( $T_{max}$ ), and half life ( $t_{1/2}$ ) for ARS, and b) the above four parameters for DHA.

The null hypothesis for each comparison is that the mean value of the endpoint does not differ between control and intervention arms. The alternative hypothesis is that the mean values of each endpoint do differ between control and intervention. Each alternative hypothesis is two-sided (ie intended to detect superiority or inferiority).

To be included in the analysis, a subject must have missed at most one of the follow-up times. Any subject in either intervention arm who did not receive all two doses of charcoal will not be included in the analysis. Any subject in the control arm who received one or more doses of charcoal will not be included in the analysis.

Following Nealon et al.(14), both one- and two-compartment models will be used for both ARS and DHA, and the better fit model will be used. The packages nlmeODE, odesolve and nlme be used with the R software (23).

Primary analysis will be by one way ANOVA on the log-transformed values of AUC and other pharmacokinetic variables. Each intervention arm will be compared to control by a contrast. If the untransformed variables have a distribution closer to normal than the log-transformed ones, then a secondary analysis will be ANOVA on the untransformed variables.

To achieve 80% power to detect a ratio of means of 1.5 of mean AUC, or other pharmacokinetic parameter, between control and either intervention arm, with coefficient of variation of 50% and two-sided significance level of 5%, we will need 23 subjects per arm (Table 2 of van Belle and Martin, 1993, American Statistician, 47: 165-167). With 30 subjects per arm, we will achieve this sample size if 20% are lost to follow-up or otherwise ineligible for inclusion in the analysis.

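### Appendix A times the PK samples from the first artesunate dose while the second dose may move by ±5 min, contradicting Sections 3.2 and 7.2.2, which time them from the second dose

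*Protocol*

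**What the plan says.** Section 3.2 lists plasma sampling at 5, 10, 15, 30, 60 and 90 min and 3 and 6 h "after the second dose of artesunate has been given (at 12 hours"). Section 7.2.2 repeats the list, ending "3 and 6 hours after the second dose of artesunate has been given". In both, the clock starts at the second dose.

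Appendix A carries an asterisk on the second-dose row and on every PK sample row, and the footnote to that asterisk says "All time points measured from the time of the first dose of IV artesunate". The second-dose row has a window of 12 h ± 5 min. The next four rows (12 h 5, 12 h 10, 12 h 15 and 12 h 30 min) have no window. The later sample rows, from 13 h on, have ±5 min.

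Group 3 charcoal shows the same split. Section 2.2 places it one hour after each artesunate dose. Appendix A places the second charcoal dose at 13 h ± 5 min, counted from the first artesunate dose.

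Section 9 states: "The primary endpoint is the area under each subject's artesunate (ARS) concentration-time curve (AUC"). On estimation it says "both one- and two-compartment models will be used for both ARS and DHA, and the better fit model will be used". It does not say whether nominal or recorded times enter the fit, and it leaves detailed methods to a separate statistical plan.

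**The concern.** The two schedules agree only when the second dose is given at exactly 12 h 00. At any other time inside the permitted window, staff can follow Appendix A to the letter and still miss the sampling times of Sections 3.2 and 7.2.2. A dose at 11 h 55 turns the 5-minute sample into a 10-minute sample; a dose at 12 h 05 makes that sample coincide with the injection.

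For most drugs a few minutes would not matter. Here the window is 5/3.1 = 1.6 half-lives in each direction, and the first few samples carry nearly all the information on artesunate AUC. Samples drawn at the wrong point cannot be recovered later.

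**Working it through.** **Inputs from the protocol.** Artesunate half-life 3.1 min (SD 1.1, so 2.0 to 4.2 at one SD) and DHA half-life 47 min (Section 2.1, Table 1). Second-dose window ±5 min (Appendix A). Ratio 1.5, CV 50%, two-sided 5%, 80% power, 23 evaluable per arm, 30 enrolled (Section 9).

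**1. The plan's own sample size.** The log-scale SD is sqrt(ln(1 + 0.5²)) = sqrt(ln 1.25) = 0.472, and the target difference is ln 1.5 = 0.405. A two-sample noncentral t calculation gives 79.4% power at 22 per arm and 81.2% at 23. The stated 23 reproduces, and 30 × 0.8 = 24 covers it. With the error variance pooled over three arms (66 and 87 degrees of freedom), power is 82% at 23 and 91% at 30. These are the baselines used below.

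**2. True time of the nominal 5-minute sample.** It is drawn at 12 h 05 from the first dose. With the second dose between 11 h 55 and 12 h 05, the true lag runs from 10 min down to 0.

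**3. Effect on AUC if nominal times are analysed.** Assume a one-compartment bolus, with k = ln 2 / 3.1 = 0.2236 per min. If the dose is given s minutes after 12 h, the concentration at nominal time t is C0·exp(−k(t − s)). A fit on nominal times returns C0·exp(ks) with k unchanged, so AUC = C0/k is multiplied by exp(ks) = 2^(s/half-life).

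| Half-life (min) | s = −5 | s = +5 |
|---|---|---|
| 2.0 | 0.18 | 5.66 |
| 3.1 | 0.33 | 3.06 |
| 4.2 | 0.44 | 2.28 |
| 47 (DHA) | 0.93 | 1.08 |

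At 3.1 min, a 2-min shift gives 0.64 to 1.56. If elapsed time is counted from the recorded second dose, the factor is 1.00 in the same model.

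**4. Illustrative effect on power (nominal times, half-life 3.1 min in everyone).** For dose times uniform over ±w, the added log-SD is k·w/√3.

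- w = 5: 0.2236 × 5/1.732 = 0.645; total sqrt(0.472² + 0.645²) = 0.800. Power for a ratio of 1.5 is about 40% at 23 per arm and 49% at 30.
- w = 2: 0.2236 × 2/1.732 = 0.258; total sqrt(0.472² + 0.258²) = 0.538. Power is about 71% and 82%.

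**5. What recorded times do not repair.** In the same model, the share of AUC that has passed before time t is 1 − 2^(−t/3.1). At 5 min this is 1 − 0.327 = 67%; at 10 min it is 1 − 0.107 = 89%. A late first sample therefore leaves more of the AUC to extrapolation, even with a correct clock in the analysis.

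**6. Group 3 charcoal.** Under Appendix A the gap from the second artesunate dose runs from 12 h 55 − 12 h 05 = 50 min to 13 h 05 − 11 h 55 = 70 min, against one hour in Section 2.2.

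**The case against.** Appendix A is headed as a summary and refers the reader to Section 7 for details, and Section 7.2.2 counts from the second dose. Section 3.2 places that dose nominally at 12 h, so 12 h 5 min could be no more than a label for 5 min after it. This is a fair reading of the intent, but the footnote is explicit and the asterisk stands on both the dose row and the sample rows. The cross-reference does not cancel it.

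A reader might infer that the conflict in itself shifts the AUC 3-fold. The documents do not support that. The shift needs a full 5-min deviation and a fit on nominal times. The protocol neither states nor rules out nominal times, and the choice is commonly left to the statistical plan, which is not at hand. The CRF is not shown either, so one cannot say that dose and draw times go unrecorded. The simple model also fails at s = +5, where the sample coincides with the injection.

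A reader might likewise take the power figures as a forecast. They rest on an assumed uniform spread of dose times and one common half-life, and they add timing variance to a 50% CV whose components the protocol does not describe.

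Finally, one might infer bias between arms in an open-label trial. Nothing shows that the second injection would be timed differently by arm: at 12 h Group 1 drinks water, Group 2 takes charcoal, and Group 3 has no oral task until 13 h. Under randomisation the expected effect is mainly noise. The Group 3 charcoal discrepancy also matters little for artesunate AUC, since 60/3.1, or about 19, half-lives have passed by one hour.

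**Conclusion.** The contradiction is real and is wrong as written: Appendix A allows the first PK sample to fall 0 to 10 min after the second dose, while Sections 3.2 and 7.2.2 require 5 min. The 3-fold change in artesunate AUC is a conditional worst case for nominal-time analysis under a one-compartment bolus model, and the power loss is an illustration under assumed dose-time spreads. DHA is hardly affected. The sample size of 23 per arm is sound on its own inputs. Analysing recorded times removes the AUC shift but not the loss of early information when the first sample is late, so the schedule itself needs correcting before dosing starts.

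**What to change.** Change the Appendix A footnote so that PK Time points 3 to 10 are timed from the second artesunate dose, in line with Sections 3.2 and 7.2.2. Record the actual time of the second injection and of each draw on the CRF, if it does not already provide for this, and state that actual elapsed times from the second dose enter the PK fit. The time anchors for Group 3 charcoal in Appendix A and Section 2.2 must be reconciled; which of them should stand is for the investigators to decide. The cost is one footnote, at most a few CRF fields, and one sentence in the protocol or statistical plan.
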